#### Secondary End Points

The secondary end points include the evaluation of many parameters (both continuous and categorical) through comparisons both between groups and within groups.

Between-group differences will be investigated with 2-tailed unpaired *t* tests (or the corresponding nonparametric Wilcoxon-Mann-Whitney tests, as appropriate) in case of a continuous variable and with chi-square test or the Fisher exact test in case of a categorical variable.

Within-group differences will be investigated with paired *t* tests (or the corresponding nonparametric Wilcoxon-Mann-Whitney tests, as appropriate) in case of a continuous variable, with the McNemar test in cases of a categorical one.

If appropriate, the percentage change with respect to the baseline value will be calculated for each interesting time point.

Global approaches, such as mixed linear models for repeated measures, will also be considered.

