**Inclusion criteria**
Age ≥18 years at the time of signing informed consent.Participants with chronic kidney disease classified as glomerular filtration rate (GFR) category G3b (30-44 mL/min/1.73 m²) or G4 (15-29 mL/min/1.73 m²); persistent albuminuria category A1 (<30 mg/g), A2 (30-300 mg/g), or A3 (>300 mg/g and <3000 mg/g).Presence of at least 1 causal etiology: diabetes, arterial hypertension, chronic glomerulonephritis, and cystic kidney diseases (eg, polycystic kidney, nephronophthisis, cortical or tubular glomerular cysts, renal medulla cystic diseases, and tuberous sclerosis).Abnormalities of kidney function (GFR and albuminuria) and structure (causal etiologies) present for >3 months with health implications.Perceived Stress Scale total score >12.Sex: male and female.Capability of giving informed consent, including compliance with requirements and restrictions.Ownership of a mobile phone, willingness to use mobile apps, and ability to download KidneYou.Native speakers of Italian or foreign individuals with a full understanding of Italian (all programs provided in Italian).

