#### Secondary End Points

The secondary end points are as follows:

To evaluate the achievement of 2 or more of the aforementioned components of the primary end pointTo assess the achievement of every single component of the primary end point in each randomized groupTo stratify the within-group changes and the between-group differences in changes of primary end point results by the eGFR category of patients with CKD (eg, G3b and G4)To stratify the within-group changes and the between-group differences in changes of primary end point results by the albuminuria category of patients with CKD (eg, A1, A2, and A3)To assess the within-group changes of mean values of azoturia (gram per 24 h) in each treatment group during the study visits (ie, V0, V2, and V3)To assess the between-group differences in changes of mean values of azoturia (gram per 24 h) during the study visits (ie, V0, V2, and V3)To assess the within-group changes of mean values of heart rate (HR), blood pressure (mm Hg), and O_2_ saturation in each treatment group during the performance of the 6-MWTsTo assess the between-group differences in changes in mean values of HR, blood pressure (mm Hg), and O_2_ saturation during the performance of the 6-MWTsTo assess the within-group changes in mean values of PA (min) self-reported by patients in each treatment group during the study visits (ie, V0, V2, and V3)To assess the within-group changes of mean values of stress reduction (according to the PSS of Cohen) in each treatment group during the study visits (ie, V0, V2, and V3)To assess the between-group differences in changes of mean values of stress reduction (according to the PSS of Cohen) during the study visits (ie, V0, V2, and V3)To assess patient satisfaction with the KidneYou App by using the Net Promoter Score system. With a score ≥7, the participant will be considered a promoter of the app

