#### Tertiary or Exploratory End Points

The tertiary or exploratory end points are as follows:

To assess the between-group differences in changes of mean values of PA (min) self-reported by patients during the study visits (ie, V0, V2, and V3)To assess the within-group changes and the between-group differences in changes of urinary levels of phosphorus, calcium, potassium, sodium, chlorine, bicarbonate, albumin, creatinine, glucose, and uric acid by urine samples during the study visits (ie, V0, V2, and V3)To assess the within-group changes and the between-group differences in changes of urinary levels of other compounds (ie, density, pH, proteins, ketones, hemoglobin, bilirubin, nitrites, white cells, red blood cells, casts, crystals, and epithelial cells) by urine samples during the study visits (ie, V0, V2, and V3)To assess the within-group changes and the between-group differences of changes in blood levels of electrolytes (potassium, sodium, chloride, and bicarbonate), minerals (phosphorus and calcium), proteins (albumin), metabolic products (nitrogen and creatinine), sugar (glucose), and uric acid in the blood samples during the study visits (ie, V0, V2, and V3)To assess the within-group changes and the between-group differences of changes of vital signs (systolic blood pressure or diastolic blood pressure, HR, and respiratory rate) during the study visits (ie, V0, V1, V2, and V3)To assess the between-group differences of changes in mean values of impedancemetry (lean mass and fat mass) during the study visits (ie, V0, V2, and V3)To assess the within-group changes and the between-group differences of changes of signs and symptoms characterizing CKD during the study visits (ie, V0, V1, V2, and V3)To assess the within-group compliance (adherence) by measuring the overall time (min) of KidneYou use during the 3 months of the studyTo assess a possible correlation between levels of compliance with KidneYou use and the rate of achievement of the primary end pointTo assess a possible correlation between levels of compliance (min) with KidneYou and the customer experience rate according to Net Promoter Score

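### Continuous end points are compared without baseline adjustment, which loses some precision, and within-group tests of perceived stress can reach significance through regression to the mean alone

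*Protocol article*

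**What the plan says.** The Statistical Analysis part headed Secondary End Points gives the methods for continuous variables. "Between-group differences will be investigated with 2-tailed unpaired" *t* tests, or Wilcoxon-Mann-Whitney tests where appropriate. "Within-group differences will be investigated with paired" *t* tests or a rank alternative. It then adds two conditional sentences: "If appropriate, the percentage change with respect to the baseline value will be calculated for each interesting time point", and "Global approaches, such as mixed linear models for repeated measures, will also be considered". No baseline covariate is named. The Tertiary or Exploratory End Points part of the Statistics section carries the same methods over.

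The list of secondary end points defines the between-group comparisons of azoturia and PSS as differences in changes over V0, V2 and V3. It also lists the within-group change as an end point of its own: "To assess the within-group changes of mean values of stress reduction (according to the PSS of Cohen) in each treatment group".

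The inclusion criteria require "Perceived Stress Scale total score >12". Under Assessments, consent, eligibility, randomisation and the PSS are all described at the baseline visit, with no separate screening visit.

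**The concern.** There are two separate issues.

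**Precision.** Each patient's V0 value is measured and usually predicts the follow-up value well. A *t* test on change subtracts that value with a fixed coefficient of 1. ANCOVA estimates the coefficient and so never has the larger variance, apart from the one degree of freedom spent. Recruitment closed at 210 participants, so the analysis is the only remaining source of precision.

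**Within-group tests on a selected outcome.** Patients enter only if their PSS is above 12. If that same score is the baseline, the mean PSS is expected to fall in both arms even if neither programme works. A paired test has no control arm to remove this. The plan gives that test a p-value and lists it as a secondary end point, so a significant fall among app users could be read as evidence for the device in a study meant to support its CE marking.

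**Working it through.** **The plan's own figure.** The article gives no calculation for continuous end points. Its sample size for the binary primary end point reproduces: two-sided α 0.05, power 0.80, 40% versus 60%, unpooled variance, n = (1.960+0.842)² × (0.40×0.60 + 0.60×0.40) / 0.20² = 7.849 × 0.48 / 0.04 = 94.2, so 95 per group. I use n = 95 per arm below only as the expected number of evaluable patients.

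**Precision, end points with no entry cut-off.** Take equal variance σ² at baseline and follow-up, with correlation ρ.

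- Change score: 2(1−ρ)σ²
- ANCOVA: (1−ρ²)σ²
- Ratio: (1+ρ)/2

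The article gives no ρ, so it is assumed:

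| ρ | ratio | variance saved | 95 / ratio |
|---|---|---|---|
| 0.5 | 0.75 | 25% | 127 |
| 0.6 | 0.80 | 20% | 119 |
| 0.7 | 0.85 | 15% | 112 |
| 0.8 | 0.90 | 10% | 106 |

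The last column is the number per arm that a change-score test would need to match ANCOVA with 95.

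**PSS, truncated at entry.** The article gives no PSS mean, SD or correlation. Assume a bivariate normal score in the source population with mean μ, SD σ and correlation ρ, no true change, and eligibility at 13 or more (cut at 12.5). Let a = (12.5−μ)/σ and λ = φ(a)/(1−Φ(a)).

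- Baseline variance after selection: V = σ²(1 + aλ − λ²)
- Expected fall with no effect: (1−ρ)σλ
- Residual (ANCOVA) variance: (1−ρ²)σ²
- Change variance: (1−ρ)²V + (1−ρ²)σ²
- Probability that the paired test is significant: noncentral *t*, 94 df, noncentrality = fall × √95 / SD of change

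Example with μ = 16, σ = 6.5, ρ = 0.7:

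- a = −0.538 and λ = 0.490
- V = 42.25 × (1 − 0.264 − 0.240) = 21.0
- Fall = 0.3 × 6.5 × 0.490 = 0.95 points
- Residual variance = 0.51 × 42.25 = 21.5
- Change variance = 0.09 × 21.0 + 21.5 = 23.4 (SD 4.84)
- ANCOVA ratio = 21.5/23.4 = 0.92
- Noncentrality = 0.955 × 9.747/4.84 = 1.92, so the paired test is significant 48% of the time

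Over the range, σ = 6.5 and ρ from 0.6 to 0.8:

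| μ | null fall (points) | paired test significant | variance saved by ANCOVA |
|---|---|---|---|
| 14 | 1.71 to 0.85 | 85% to 54% | 9% to 4% |
| 16 | 1.27 to 0.64 | 61% to 34% | 11% to 5% |
| 18 | 0.91 to 0.45 | 35% to 19% | 13% to 6% |
| 22 | 0.38 to 0.19 | 10% to 7% | 16% to 8% |

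**The randomised comparison.** I also simulated 3,000 trials with no effect in each of three settings and tested change between arms.

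| μ, σ, ρ | between-group type I error | significant within an arm | significant in one arm only |
|---|---|---|---|
| 16, 7, 0.6 | 5.6% | 64% | 46% |
| 19, 6, 0.7 | 4.7% | 15% | 28% |
| 22, 6, 0.8 | 4.6% | 7% | 13% |

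The between-group test stays close to its nominal 5%. The last column shows how often the within-group tests would suggest a contrast between arms that does not exist.

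**The case against.** The strongest defence is that the planned comparison is sound. The end points are changes from V0, so a reader who infers that the baseline is thrown away would be wrong: it is used, only less efficiently. In a randomised trial the change-score test is valid, and no continuous end point was powered, so the lost precision is not a shortfall against any stated target. This stands, and it limits the first issue to efficiency.

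A reader might also infer that the entry rule makes the within-group stress reduction significant. The article does not support that. It gives no PSS distribution, and well above the cut-off the probability falls to 7–10%. Nor does it say whether the qualifying score is the analysed V0 value or is repeated after enrolment; a separate measurement would weaken or remove the effect. For PSS and azoturia the between-group comparison is listed beside the within-group one, and no success criterion hangs on a within-group p-value. All of this stands. It makes the claim one of possibility, but does not make the paired test informative about the device.

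Model detail is often left to an analysis plan. Here, however, the article names the tests and puts the mixed model second, so the point concerns a stated choice.

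Physical activity minutes invite a further step. The article lists "within-group changes in mean values of PA (min) self-reported by patients in each treatment group" as secondary, but the randomised comparison, "To assess the between-group differences in changes of mean values of PA (min) self-reported by patients during the study visits", as exploratory. Promoting the latter is a preference rather than a correction. Minutes are self-reported and the programme is delivered by app in one arm and paper diary in the other, so recording may differ by arm and an exploratory rank is defensible.

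**Conclusion.** The point holds as a moderate one about efficiency and reporting for secondary and exploratory end points. The planned between-group test is valid but gives up about 10–25% of variance for end points with no entry cut-off (assumed ρ 0.5–0.8), and about 4–13% for PSS (assumed source mean 14–18, SD 6.5, ρ 0.6–0.8). The within-group PSS test has a probability of about 7% to 85% of being significant with no effect, for source means from 22 down to 14, if the qualifying score is the V0 baseline. Its result is therefore not evidence that the app works.

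A reader might infer that regression to the mean also distorts the trial's main conclusion. It does not. It is expected equally in both randomised arms, the between-group comparison keeps its error rate, and the primary chi-square or Fisher test on the composite is not biased by it.

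**What to change.** 1. For continuous secondary and exploratory end points, make the main between-group analysis an ANCOVA with the baseline value as covariate, or a repeated-measures mixed model over V2 and V3 with the baseline value as covariate, arm, visit and arm-by-visit. Keep the unpaired *t* test as a sensitivity check.
2. Report within-group changes as means with 95% confidence intervals and no p-values, and draw no efficacy conclusion from them.
3. State whether the PSS that qualifies a patient is also the V0 value analysed.
4. Leave between-group physical activity minutes exploratory.

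The cost is wording and modest programming, with no new data. The Results section says analysis is ongoing, and the trial is open label. The change should therefore be dated and its timing stated relative to access to outcome data by arm. If that access has already occurred, label the adjusted analysis post hoc and report it beside the planned *t* test. Dropping the within-group p-values is possible at any stage.

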### Statistics

#### Sample Size Calculation

This study is designed to test the null hypothesis that the percentage *success* (defined by the achievement of at least one of the 3 conditions described in the primary end point, with no hierarchical structure among them) in KidneYou nonusers is equal to the percentage “success” in KidneYou users. The alternative hypothesis is that the percentage “success” in KidneYou nonusers is different from the percentage “success” in KidneYou users.

The sample size is estimated to assess the study hypothesis on the primary end point.

The sample size calculation is based on the combination of the expected proportion of success in the control group and the expected delta (Δ) of success in the experimental group.

With a significance level α equal to .05 and a power equal to 80%, a sample size of 190 participants (95 per group) is required to detect as significant, if any, a success delta in favor of the experimental group equal to 20% (under the hypothesis of success rate of 40% in the control group and success rate of 60% in the experimental group). Considering a dropout rate of approximately 10%, a total of 210 patients (105 per group) will have to be enrolled. A competitive enrollment approach across the centers involved in the study will be used to reach the sample size efficiently.

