#### Tertiary or Exploratory End Points

Tertiary or exploratory end points that involve a comparison between and within groups will be analyzed as described in the “Secondary End Points” section.

To assess possible correlation between levels of compliance to KidneYou use and other parameters of interest, the most appropriate test will be used. In particular, in case of continuous or numerical parameters, the Pearson correlation coefficient (or Spearman, as appropriate) will be computed; in case of discrete or dichotomous parameters, the association will be assessed with 2-tailed unpaired *t* tests or the corresponding nonparametric Wilcoxon-Mann-Whitney tests, as appropriate.

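### The plan names Wilcoxon-Mann-Whitney as the rank-based counterpart of the paired t test for within-group change; that test ignores the pairing and, under the usual positive within-patient correlation, would miss real changes

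*Protocol article*

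**What the plan says.** The Secondary End Points section under Statistics in the protocol article gives two rules for continuous variables.

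- Between groups: "Between-group differences will be investigated with 2-tailed unpaired" t tests, with Wilcoxon-Mann-Whitney as the nonparametric alternative.
- Within groups: the sentence names the paired t test first and then gives this alternative: "or the corresponding nonparametric Wilcoxon-Mann-Whitney tests, as appropriate) in case of a continuous variable, with the McNemar test in cases of a categorical one".

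The same rank test therefore stands as the counterpart of both the unpaired and the paired t test. The section ends with an optional addition: "Global approaches, such as mixed linear models for repeated measures, will also be considered".

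The next section, Tertiary or Exploratory End Points, carries the rules over: "Tertiary or exploratory end points that involve a comparison between and within groups will be analyzed as described in the" preceding section.

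The outcomes concerned are listed under Main Objectives and End Points. A typical secondary one reads "To assess the within-group changes of mean values of azoturia (gram per 24 h) in each treatment group during the study visits", with V0, V2 and V3 as the visits.

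**The concern.** A within-group change compares the same patients at two visits. The paired t test works on each patient's difference, and so does its rank-based counterpart, the Wilcoxon signed-rank test. Wilcoxon-Mann-Whitney pools the values, ranks them as if they came from two separate sets of people, and takes its standard error on that footing. When the two values of a patient are positively correlated, that standard error is too large.

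The outcomes exposed are the within-group secondary end points: azoturia, PSS, self-reported activity minutes, and heart rate, blood pressure and oxygen saturation during the 6-minute walk test. The exploratory within-group comparisons of urine, blood and vital signs are exposed as well. For activity minutes the between-group comparison is only exploratory, so the within-group test is the sole secondary-level analysis of that outcome. Duration data of this kind are often skewed enough to send an analyst to the nonparametric option.

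**Working it through.** **1. The text set side by side**

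| Comparison | Data | Parametric test named | Rank test named | Categorical test named |
|---|---|---|---|---|
| Between groups | Independent | Unpaired t | Wilcoxon-Mann-Whitney (correct) | Chi-square or Fisher (independent samples) |
| Within groups | Paired | Paired t | Wilcoxon-Mann-Whitney (wrong) | McNemar (paired) |

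Only the rank test in the second row fails to match its data. No other part of the article corrects it.

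**2. The plan's own figure**

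The Sample Size Calculation section states: "With a significance level α equal to .05 and a power equal to 80%, a sample size of 190 participants (95 per group) is required", for success rates of 40% and 60%. With unpooled variance:

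n per group = (1.960 + 0.842)² × (0.4 × 0.6 + 0.6 × 0.4) / 0.20² = 7.849 × 0.48 / 0.04 = 94.2, so 95 per group and 190 in total.

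The figure is reproduced. It concerns the primary between-group proportion and does not depend on the point raised here. It serves only to set the number of pairs per arm at 95.

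**3. Why the error runs in one direction**

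In large samples, pairing multiplies the null variance of the Mann-Whitney statistic by (1 − r), where r is the rank correlation between a patient's two values. For bivariate normal data, r = (6/π) × arcsin(ρ/2). The test still uses the variance for independent samples, so its real critical value is 1.96/√(1 − r).

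- ρ = 0.3: r = 0.288, √(1 − r) = 0.844, critical value 2.32, two-sided error 2.0%.
- ρ = 0.5: r = 0.483, √(1 − r) = 0.719, critical value 2.72, two-sided error 0.6%.
- ρ = 0.7: r = 0.683, √(1 − r) = 0.563, critical value 3.48, two-sided error 0.05%.

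A positive correlation always pushes the error below 5%.

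**4. Simulation**

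The settings were 95 normal pairs, 10,000 replicates per setting and two-sided 5%. The documents give neither the within-patient correlation nor the size of change. Both are assumptions, so the correlation is shown over a range.

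| Assumed correlation | Type I error, Mann-Whitney | Type I error, signed-rank | Power at 0.25 SD, Mann-Whitney | Power at 0.25 SD, signed-rank |
|---|---|---|---|---|
| 0 | 4.9% | 4.8% | 39% | 38% |
| 0.3 | 2.0% | 5.1% | 37% | 52% |
| 0.5 | 0.8% | 5.0% | 34% | 65% |
| 0.7 | 0.02% | 4.9% | 32% | 86% |
| 0.9 | 0.0% | 4.9% | 22% | 99.9% |

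The simulated error rates agree with the approximation in step 3. At correlation 0.7 both are below 0.1%.

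**The case against.** The strongest reply is that this is a slip of wording. The sentence starts from paired t tests, asks for the corresponding rank test and adds McNemar, so the authors plainly had paired data in mind. The parenthesis looks repeated from the paragraph before. That is likely, but the text still names a specific test, and a programmer who follows it would run a rank-sum procedure on paired data. It is also not a detail left to the SAP, because the article has already fixed it.

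A second reply is that the reach is narrow. This stands. The test is a conditional fallback for continuous within-group comparisons that are secondary or exploratory. Change within one arm is not the randomized comparison.

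A third reply is that the simulation uses normal data, for which the paired t test would be chosen and the fallback never reached. This stands in part. The Mann-Whitney error rates depend only on ranks, so they carry over unchanged to any skewed variable that is an increasing transformation of such pairs, the same at both visits. The signed-rank power figures do not carry over in this way and are illustrative.

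Mixed models do not remove the problem. They are only to be considered, and they do not replace the named test.

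A reader might infer that the error could produce false claims of benefit, or that every non-normal within-group end point is bound to get an invalid p-value. The documents support neither reading. Under positive correlation the test is conservative. The fallback applies only where judged appropriate, and the intended test may be the right one despite the wording.

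**Conclusion.** The plan is wrong as written and should be corrected, but it is not a threat to the trial's main conclusion. If the sentence is followed, within-group changes tested by ranks get p-values that are too large. The loss depends on the correlation: none at 0, and at 0.5 power of about 34% against 65% for a 0.25 SD shift. These figures rest on assumed correlations, normal data, an assumed shift and 95 complete pairs per arm.

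The direction rests only on the correlation being positive, which is the usual case for repeated measurements in the same patients. The primary chi-square or Fisher analysis, the between-group tests and the sample size of 190 (210 with dropout) do not change.

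**What to change.** In the within-group sentence of the Secondary End Points section under Statistics, replace Wilcoxon-Mann-Whitney with Wilcoxon signed-rank. Keep Wilcoxon-Mann-Whitney in the between-group sentence. The exploratory section refers back to this one and needs no edit of its own. No new rule for choosing between the parametric and the rank test is needed to correct the error.

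Then check that the SAP and the SAS code run a signed-rank test on each patient's difference. The article describes data analysis as ongoing, so this check should come before the within-group results are finalized. The cost is one phrase and a look at the code. No data, sample size or primary result changes, and there is no statistical drawback.
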